#### Sleep

Objective sleep duration and sleep efficiency will be measured using the SenseWear Mini [50]. Sleep quality will be assessed using the 19-item Pittsburgh Sleep Quality Index [51], a commonly used subjective sleep questionnaire. Participants will also keep a self-report sleep diary which will be used to confirm sleep windows calculated from the SenseWear Mini. The STOP-Bang questionnaire will be used to screen for risk of obstructive sleep apnea at baseline [52].

#### Falls

Falls will be prospectively documented by all participants on a monthly basis via calendars provided by the research team. Participants will be asked to report any falls directly to the research team after they occur. We will complete a follow-up falls interview over the phone to obtain information regarding the fall and determine if any adjustments to the study protocol and interventions are required.

#### Health resource utilization (HRU)

Cost data will be collected monthly via HRU diaries, and these self-report cost diaries will be confirmed during in person assessments or via telephone calls every 3 months using the HRU questionnaire [53], which is based on validated cost questionnaires [54–56]. The HRU questionnaire is utilized to collect specific details on (1) health professional visits; (2) hospital, rehabilitation facility, and inpatient clinic visits; (3) laboratory procedures or investigations; and (4) medications. Using a fully allocated hospital cost model (for in-patient costs) and the British Columbia provincial guide to medical fees (for outpatient costs), we will assign health care resource utilization on a per participant basis. Evidence from a systematic review of 15 studies demonstrates good agreement between self-reported questionnaires on resources utilization and administrative data [57].

#### Intervention adherence

Adherence to the intervention will be measured as session attendance (HC and ED groups). Session attendance will be recorded by health coaches and education session leaders and will be estimated as the percentage of total sessions attended.

### Participant timeline {13}

Participant enrolment began July 2023 and the first participant was randomized September 5, 2023. We expect participant recruitment, assessments, and follow-up visits to be completed by October 2026. Participants will undergo a phone screening to determine preliminary eligibility. If appropriate, participants will be invited for an in-person screening. Within 1 month of the in-person screening, participants will complete the remainder of the baseline assessments and will be randomized to either the HC or ED group. Participants will partake in intervention procedures for 26 weeks. Upon completing the intervention, participants will be followed for another 26 weeks. Upon the final follow-up assessment at 52 weeks, participants in the ED group will receive an initial HC visit followed by 2 additional HC calls and receive access to exercise-related materials. The participant timeline of assessments is shown in Table 2.

**Table 2 Tab2:**
[figure not shown]
Participant timeline of assessments

*Falls data will be collected monthly throughout the trial

### Sample size {14}

The sample size for this study is 290 participants, based on SPPB data published in the LIFE study that examined changes in SPPB scores based on changes in MVPA [6]. At 6 months, those in the highest quartile of MVPA change (i.e., > 43 min per week) experienced a mean improvement (calculated as 6 months minus baseline) of 1.21 in SPPB score with a SD = 0.98. A 0.5 difference in SPPB score is considered a clinically meaningful change [58]. Assuming at least 90% of our HC participants will increase their participation in MVPA by at least 50 min per week, and splitting the remaining 10% of HC participants equally among the 3rd quartile in MVPA change (mean SPPB change = 1.16) and the 2nd quartile in MVPA change (mean SPPB change = 0.89), we anticipate a mean SPPB improvement of 0.90 × 1.21 + 0.05 × 1.16 + 0.05 × 0.89 = 1.19 in the HC group. For the ED group, we assume the mean SPPB change will be similar to what was observed in the LIFE study control group [6]; we calculated this value to be 0.84 from the published data. Thus, the effect size for the SPPB outcome is (1.19 − 0.84)/0.98 = 0.36.

Using a two-tailed test alpha = 0.05, our estimated effect size requires a sample size of 246 participants (123 per group) in order to achieve 80% power, assuming the outcomes for all participants are independent. In principle, this sample size should be adjusted by a design effect (DE) to account for the nesting of participants within coaches in the HC arm and nesting of participants within cohorts in the ED arm. However, as noted in the description of the HC intervention, the ICC in a previous study was found to be only 0.0007 [17]. Together with an expected 15 participants per coach, the DE is only 1 + (15 − 1) × 0.007 = 1.01 which implies a negligible impact on the required sample size. No data are available on the ICC within ED groups, but we expect it to be low enough to also have negligible impact. Allowing for a 15% dropout rate leads to the sample size of 290 participants (i.e., 145/group).

### Recruitment {15}

We will recruit participants from 2 committed clinics: (1) Vancouver General Hospital (VGH) Falls Prevention Clinic and (2) VGH Geriatric Internal Medicine Teaching Clinic. Additionally, we will recruit participants through word of mouth, public talks, and advertisements place in community centers and newspapers. We have an established track record of recruiting older adults, including those with mobility limitations, for behavioral RCTs.

## Assignment of interventions: allocation

### Sequence generation {16a}

Participants will be allocated to experimental groups (1:1 ratio) in blocks formed by sequentially enrolled participants. Block sizes may vary to accommodate varying recruitment rates over time and ensure participants receive timely intervention. Participants within each block are randomized into ED to form a cohort for the group education sessions. The allocations will be generated in 'R' using a fixed seed to ensure reproducibility of the random sequence.

### Concealment mechanism {16b}

When a block has been filled, the study coordinator will send the participant study identifiers (ID) to the study statistician, who is not involved in the RCT. The statistician will attach the allocations and return the list to the study coordinator.

### Implementation {16c}

Upon completion of the baseline assessments, the study coordinator will reveal which experimental group participants are been assigned to for scheduling purposes.

## Assignment of interventions: blinding

### Who will be blinded {17a}

Assessments will be performed by blinded study personnel who are not involved in the HC or ED interventions or study enrolment. Blinding of participants will not be feasible. Participants will be reminded to not discuss or disclose their study activities with assessors.

### Procedure for unblinding if needed {17b}

N/A. There is no indication of unblinding for the assessors.

## Data collection and management

### Plans for assessment and collection of outcomes {18a}

Research personnel will be trained in all primary and secondary outcome measure collection to minimize intra- and inter-rater variations. Outcomes will be collected at 4 time points throughout the trial: (1) baseline (at enrolment), (2) midpoint (13 weeks), (3) final (26 weeks), and (4) follow-up (52 weeks).

### Plans to promote participant retention and complete follow-up {18b}

Participants in the HC group will have regular communication from bi-monthly to monthly sessions with their BAP coach to promote retention and adherence to the intervention. Participants in the ED group will have the same structure of engagement with group education sessions to promote retention and adherence. Education session attendance will be incentivized by entering participants into a gift card drawing every other session. Throughout the study intervention and follow-up time frame, participants will receive monthly communication from study personnel to assess falls and other outcomes. In a previous study utilizing a similar HC protocol in adults with mild cognitive impairment, adherence rates to PA recommendations with ≥ 73% and attrition rates were ≤ 10.4% [59, 60].

### Data management {19}

Data will be managed using Research Electronic Data Capture (REDCap) which is a secure web-based application. Data will be entered by trained study personnel who will conduct range checks for data values to ensure quality.

### Confidentiality {27}

Only the PI and approved study personnel will have access to the data and no unauthorized personnel will be able to access the data. Physical copies of data will be stored in a secured and locked location, and electronic documents will be stored on a secured server. All participant data will be associated with an identification code and not by personal name or details. There will be one document that maps participant names to their identifier, which will be stored securely on the server and password protected so that only the PI and research coordinator will have access to this information.

### Plans for collection, laboratory evaluation and storage of biological specimens for genetic or molecular analysis in this trial/future use {33}

Research blood will be collected in a subset of participants, based on funding. The analytes of interest will include neurotrophic factors, myokines, sex steroid hormones, and pro- and anti-inflammatory cytokines. Whole blood, serum, and plasma will be processed and stored at − 80 °C in a secure research facility. Remaining blood samples will be stored for 5 years from collection and then destroyed.

## Statistical methods

### Statistical methods for primary and secondary outcomes {20a}

All primary and secondary analysis will follow the intent to treat principle. Participants who have been randomized will be included in all analysis to estimate intervention effects irrespective of deviations from the intervention protocol [61]. The primary outcome (SPPB) will be modeled using a three-level linear mixed model that includes random intercepts at the coach and the participant levels (for the HC group) or the education cohort and the participant levels (for the ED group), fixed effects of time, experimental group (HC vs. ED), and the group-by-time interactions. The treatment effect will be estimated as the difference in mean change in outcome between the two arms, calculated using the fitted model coefficients. Secondary outcomes will be analyzed using analogous linear mixed models. All linear mixed models will be adjusted for baseline outcome score and baseline characteristics. The proportion of participants able to complete the 400-m walk at trial completion and at 6-month follow-up will be compared using a two-level (clusterd by coach in the HC group, clusterd by cohort in the ED group) logistic mixed model for binary outcomes. A pre-specified statistical analysis plan will be developed prior to the release of data for analysis.

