### Objectives {7}

The primary aim of the SuPA Mobility Trial is to assess if a 26-week HC intervention that aims to increase time spent in moderate to vigorous PA (MVPA) by at least 50 min per week can improve mobility, as measured by the SPPB, versus a 26-week health education (ED) program in older adults with mobility limitations. Our secondary objectives are to evaluate the effects of HC compared with ED in the following outcomes: (i) time spent in MVPA and average daily awake sedentary time, (ii) 4-m walk gait speed, (iii) the capacity to complete a 400-m walk in ≤ 15 min (yes/no), (iv) cognitive function, (v) community mobility, (vi) fatigue, (vii) muscle strength, (viii) mood, (ix) quality of life, and (x) sleep. We will also perform a 26-week follow-up assessment to determine whether the benefits of HC versus ED persist 6 months after cessation of the intervention. Additionally, we will perform a concurrent economic evaluation to determine whether HC compared with ED is cost-effective at intervention cessation and follow-up.

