### Methods in analysis to handle protocol non-adherence and any statistical methods to handle missing data {20c}

Missing outcome data will not be imputed since estimates from linear mixed models are fully efficient if the missing data are missing at random [63]. If we encounter more than 10% missing outcome data, we will consider plausible explanations for why the data may not be missing at random and assess the sensitivity of the results by fitting a joint model that incorporates non-ignorable dropout [64]. Missing covariate data will be multiply imputed assuming they are missing at random, unless there is a clear rationale for treating them otherwise.

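### With only a random intercept within participant, the mixed model may understate the 52-week standard error if correlation falls with time between visits

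*Protocol article*

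**What the plan says.** Section {20a} of the protocol article specifies a "three-level linear mixed model that includes random intercepts at the coach and the participant levels" for the HC arm, "or the education cohort and the participant levels (for the ED group"). The fixed part has "fixed effects of time, experimental group (HC vs. ED), and the group-by-time interactions". On the estimand it says "The treatment effect will be estimated as the difference in mean change in outcome between the two arms", and on covariates "All linear mixed models will be adjusted for baseline outcome score and baseline characteristics". Continuous secondary outcomes get models of the same kind. The section names no random slope, residual correlation or visit-specific variance, and closes with "A pre-specified statistical analysis plan will be developed prior to the release of data for analysis".

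Two other places depend on this model. The objectives section {7} announces a later assessment "to determine whether the benefits of HC versus ED persist 6 months after cessation of the intervention". The missing-data section {20c} declines to impute outcomes because "estimates from linear mixed models are fully efficient if the missing data are missing at random".

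**The concern.** The coach or cohort intercept takes the same value at all of a participant's visits, so it cannot make correlation fade over time. The only other named source of correlation is the participant intercept. Read in the ordinary way, with independent residuals of equal variance, the model is compound symmetric. Baseline correlates with week 13 exactly as strongly as with week 52, and every visit has the same variance.

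That is a strong assumption here. The visits are unequally spaced and the intervention ends at week 26. Entry also requires an SPPB of 9 or less, which restricts the baseline spread but not the later spread. If correlation does fall with time apart, one averaged standard error serves every visit: too large at 13 weeks, about right at 26 and too small at 52. At stake is the test of persistence at 52 weeks, for the SPPB and for continuous secondary outcomes measured then.

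The missing-data argument is also affected. Full efficiency, and valid likelihood inference when data are missing at random, presuppose a correctly specified covariance. I have not put a number on that part.

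**Working it through.** **Inputs.** Visits at 0, 13, 26 and 52 weeks (Outcomes {12}); two-sided alpha 0.05 (Sample size {14}); random and fixed effects as quoted from {20a}. The article gives no SPPB correlations and no visit SDs over 52 weeks. Every covariance below is assumed.

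**1. The plan's own figure.** Per arm, n = 2(1.960 + 0.842)²/d² + 1.960²/4.
- d = 0.36: 121.1 + 0.96 = 122.1.
- Unrounded d = 0.35/0.98 = 0.357: 123.1 + 0.96 = 124.0.
- The article states 123, or 246 in total; 246/0.85 = 289.4, hence 290.

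The figure reproduces. It rests on the six-month change alone, so nothing below alters it.

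**2. Formula, baseline as one of four responses (reading A).** With unit variances, the compound-symmetry model reports a variance of change proportional to 1 − r̄ at every visit, where r̄ is the mean of the six pairwise correlations. The true variance of change to visit t is proportional to 1 − r(0,t). So:
- reported SE / true SE = √[(1 − r̄)/(1 − r(0,t))]
- type I error = 2[1 − Φ(1.96 × ratio)]

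**3. Pure geometric decay, 0.85 per 13 weeks.** The correlations are 0.850 (0–13 and 13–26), 0.7225 (0–26 and 26–52), 0.614 (13–52) and 0.522 (0–52), so r̄ = 0.714.
- 26 weeks: √(0.2865/0.2775) = 1.016; type I error 4.6%.
- 52 weeks: √(0.2865/0.4780) = 0.774; type I error 12.9%.

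**4. Stable person effect and measurement error.** Take 30% person variance, 50% decaying at 0.8 per 26 weeks, and 20% error. The decaying part alone has mean correlation 0.791, so r̄ = 0.30 + 0.50 × 0.791 = 0.695. Also r(0,26) = 0.30 + 0.50 × 0.80 = 0.70 and r(0,52) = 0.30 + 0.50 × 0.64 = 0.62.
- 26 weeks: √(0.3046/0.30) = 1.008; 4.8%.
- 52 weeks: √(0.3046/0.38) = 0.895; 7.9%.

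**5. Same structure, baseline as covariate only (reading B).** The common slope b is the mean of 0.747, 0.70 and 0.62, which is 0.689. The residual variance at t is 1 + b² − 2b·r(0,t): 0.445, 0.510 and 0.620 at 13, 26 and 52 weeks. The model reports their mean, 0.525.
- 26 weeks: √(0.525/0.510) = 1.015; 4.7%.
- 52 weeks: √(0.525/0.620) = 0.920; 7.1%.

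**6. Range over scenarios.** Each row spans both readings.

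| Assumed truth | 52-week SE ratio | 52-week type I error | 26-week type I error |
|---|---|---|---|
| Equal correlation 0.6 | 1.00 | 5.0% | 5.0% |
| 30% person, 50% decaying (0.7–0.9 per 26 weeks), 20% error | 0.88–0.94 | 6.5–8.4% | 4.7–4.9% |
| Random intercept and slope | 0.88–1.00 | 4.9–8.3% | 4.0–4.9% |
| Pure geometric decay, 0.6–0.9 per 26 weeks | 0.75–0.85 | 9.5–14.2% | 3.7–4.9% |
| Correlation 0.6; SDs 1, 1.1, 1.1, 0.9 | 1.08–1.15 | 2.4–3.4% | about 5.5–6.4% |

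Other mixes of person effect, decay and error gave about 6–9% at 52 weeks. The least favourable had 40% person variance, 0.85 per 13 weeks and only 10% error, under reading A, and reached 9.7%.

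**7. Entry cut-off.** With the baseline SD set to 0.7 of the later SD, reading A falls from 13.5% to 10.9% under decay of 0.8 per 26 weeks, and from 5.0% to 3.9% under equal correlation. Reading B is unchanged. The cut-off makes equal variance doubtful but does not worsen the 52-week inflation.

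**8. Direct 26-versus-52-week contrast.** The SE ratio is 0.95–1.03 in all scenarios tried.

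These closed forms assume complete, balanced data and leave out coach and cohort variation.

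**The case against.** The strongest reply is that the article leaves residual covariance, robust standard errors and degrees of freedom to the announced analysis plan. A model with these random intercepts can still carry an autoregressive or heterogeneous residual structure, so nothing is strictly forced. That stands as a limit on the wording: compound symmetry follows only with the usual independent, equal-variance residuals. It does not dispose of the point. The article states its dependence structure, and an analysis plan that follows it to the letter would carry the restriction forward.

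The second reply concerns size. A reader might infer that the 52-week tests will run at 12–14% error. The documents do not support this. That figure needs pure geometric decay, no stable person effect, no measurement error, and baseline treated as a response. The article says every linear mixed model is adjusted for the baseline score, and with baseline as covariate the same decay gives about 10–12%. A stable person effect and some error in a performance test are both plausible, and bring it to about 6–9%. If variance falls at 52 weeks the error goes the other way.

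A reader might also infer that the model has one random intercept in all, or that the primary result is compromised. The coach and cohort intercepts are stated in the same sentence. The sample size rests on the six-month change, and that contrast is near nominal under decay.

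**Conclusion.** The point holds in conditional form. Within a participant the article names only a random intercept. With independent, equal-variance residuals, this makes the 52-week standard error depend on an assumption of equal correlation and variance that the design gives little reason to expect.

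If correlation falls with time apart, the 52-week SE is too small by about 6–12% in the tabulated person-effect scenarios and 15–25% under pure geometric decay. The 26-week contrast becomes mildly anti-conservative only in the example with lower variance at 52 weeks, and there the 52-week test is conservative.

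The harm therefore falls mainly on the secondary comparison of change from baseline at 52 weeks, for the SPPB and the analogous secondary models. It is worth correcting because the correction is cheap, not because an error rate has been demonstrated. Confidence is moderate, since all the ranges rest on assumed covariances.

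**What to change.** In the analysis plan, keep the coach and cohort random effects and replace the participant random intercept with an unstructured within-participant covariance across visits. Name a fallback, such as heterogeneous Toeplitz, if the model does not converge. Apply the same rule to the SPPB and to the analogous models for continuous secondary outcomes.

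The cost is one model statement. The covariance has 4 × 5/2 = 10 parameters with four visits as responses, or 3 × 4/2 = 6 if baseline is only a covariate. Outcomes also collected by telephone at 39 weeks would need 5 × 6/2 = 15 or 4 × 5/2 = 10 if that visit is modelled. With 290 participants this should be estimable. The downside is these few extra parameters and a small risk of non-convergence, which the fallback covers. The article places the analysis plan before data release, so the change can still be pre-specified.

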## Discussion

Previous research has demonstrated the importance of MVPA on improving mobility and reducing MMD risk in older adults with mobility limitations. However, there is a need to identify strategies that can be delivered at scale for this population. The proposed research will utilize a novel HC intervention to promote MVPA by a minimum effective dose in older adults with mobility limitations. The findings of this study will provide insights on the effect of a HC intervention on mobility in older adults with mobility limitations and thus, at risk for MMD. This study will evaluate effects of HC on secondary health outcomes, including PA levels, gait speed, 400-m walk, cognitive function, fatigue, strength, functional and community mobility, mood, quality of life, sleep, and falls. Finally, this study will provide an estimate of the cost-effectiveness of the HC intervention. These findings have the potential to reduce the personal and societal burden of limited mobility and MMD via a strategy that can be widely implemented.

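### Read literally, the analysis section applies a baseline-adjusted linear model of mean change to falls, a sparse event outcome recorded on monthly calendars; falls should be excepted and its status made consistent

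*Protocol article*

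**What the plan says.** **Status of falls.** The Discussion opens its list of secondary endpoints with "This study will evaluate effects of HC on secondary health outcomes, including PA levels, gait speed, 400-m walk, cognitive function, fatigue, strength" and closes it with "functional and community mobility, mood, quality of life, sleep, and falls". The Falls entry also stands under the Secondary outcomes heading. The secondary objectives in Objectives {7} list ten domains, (i) to (x), and falls is not one of them.

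**How falls are recorded.** The Falls entry states: "Falls will be prospectively documented by all participants on a monthly basis via calendars provided by the research team". The footnote to Table 2 gives falls a schedule of its own: "Falls data will be collected monthly throughout the trial".

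**Analysis.** Section {20a} describes a linear mixed model for the Short Physical Performance Battery (SPPB) and then extends it: "Secondary outcomes will be analyzed using analogous linear mixed models". It adds "All linear mixed models will be adjusted for baseline outcome score and baseline characteristics", and defines the effect thus: "The treatment effect will be estimated as the difference in mean change in outcome between the two arms, calculated using the fitted model coefficients". The one departure is for the 400-m walk, which receives a "logistic mixed model for binary outcomes". No section names a rate, count or time-to-event method for falls.

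**The concern.** The rule in {20a} suits scores measured at each visit, such as gait speed or the fatigue scale. Falls is an event outcome that accrues over time at risk. Most person-months will contain no fall, the variance rises with the mean, and follow-up length differs between participants who stay and those who leave. A normal-error model of change represents none of this, and the plan describes no calendar record before randomisation from which a change could be taken.

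The authors departed from the linear rule where a data type clearly did not fit it, for the binary 400-m walk, but made no such departure for falls. This goes beyond detail left to the statistical analysis plan (SAP), because a method is stated and its scope includes falls.

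At stake is the between-group falls comparison, which matters in a trial that promotes physical activity in people with limited mobility and recruits partly from a falls prevention clinic (Recruitment {15}). A later change of model, however sensible, would also look like an unexplained departure from the published rule.

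**Working it through.** **1. The plan's own figure.** The only sample size stated is for SPPB. With effect size 0.36, two-sided alpha 0.05 and 80% power (Sample size {14}), a two-sample t-test needs 122.09, so 123 per group and 246 in total. Allowing for 15% dropout, 123/(1 − 0.15) = 144.7, so 145 per group and 290 in total. Both stated figures reproduce and neither depends on falls. No figure is stated for falls.

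**2. Does the linear rule reach falls?**
- The Discussion makes falls a secondary outcome.
- The sentence on secondary outcomes in {20a} carries no qualification.
- The only exception in {20a} is the 400-m walk.
- No other section gives falls a method.

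So, on its wording, the rule reaches falls.

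**3. Does the model suit the record?** The model needs a baseline score and a change. The Falls entry and the Table 2 footnote describe prospective monthly recording. Outcomes {12} says generally that every outcome is measured at baseline, and the body of Table 2 is not shown, so a baseline fall history cannot be excluded. A recalled history would still not be the same measure as a prospective calendar record. Whether the endpoint is the number of falls, a rate or any fall is not stated.

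**4. How sparse would the data be?** The documents give no fall rate or dispersion, so both are **assumptions**: rate r from 0.5 to 2 falls per person-year and negative binomial dispersion k from 0.5 to 2. The mean is m = r/12 for a month and m = r/2 for 26 weeks.

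- Probability of zero: (1 + k·m)^(−1/k)
- Skewness: (1 + 2·k·m)/√(m + k·m²)

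| r | k | monthly zero | monthly skewness | 26-week zero | 26-week skewness |
|---|---|---|---|---|---|
| 0.5 | 0.5 | 0.960 | 5.05 | 0.790 | 2.36 |
| 0.5 | 2 | 0.961 | 5.49 | 0.816 | 3.27 |
| 1 | 1 | 0.923 | 3.88 | 0.667 | 2.31 |
| 2 | 0.5 | 0.852 | 2.75 | 0.444 | 1.63 |
| 2 | 2 | 0.866 | 3.54 | 0.577 | 2.89 |

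Worked example, r = 1 and k = 1, monthly: 1/(1 + 1/12) = 0.923.

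Across the grid, 85% to 96% of monthly values are zero (skewness about 2.8 to 5.5), as are 44% to 82% of 26-week totals (skewness about 1.6 to 3.3). The poor fit does not hinge on any one choice of rate or dispersion.

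**5. Does sparsity invalidate a comparison of means?** Welch tests were simulated on negative binomial totals with 123 per group, complete follow-up, no true difference, means 0.25 to 1 and dispersion 0.5 to 2 (20,000 replicates each). Type I error was about 4.7% to 5.3%. The simulation ignores clustering and repeated measures, but it shows that non-normality alone does not make a simple comparison of means misleading at this size.

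**The case against.** Several counter-arguments have force.

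- **The assignment is inferred.** Section {20a} does not mention falls, and Objectives {7} omits it. Position under the Secondary outcomes heading proves little, because health resource utilization and adherence sit there too, and resource use is analysed in the economic evaluation of {20b}. The Discussion sentence is the firm support. It is explicit, so the point stands, but the inconsistent status of falls is part of the defect.
- **An SAP is announced** in {20a}, and the distribution for one secondary outcome is often settled there. This limits the severity. It does not remove the point, because a general method is already stated and it covers falls.
- **A reader might infer that the model cannot be fitted because falls has no baseline value.** The documents do not support that: {12} says all outcomes are assessed at baseline, and the body of Table 2 is missing from the text at hand.
- **A reader might infer that the falls comparison would be invalid, or biased by unequal dropout.** A difference in mean falls is a legitimate quantity under randomisation, and the simulation shows no inflated error with complete follow-up. Dropout bias would arise from per-person totals analysed without follow-up time, which no section proposes. A repeated-measures model analogous to the SPPB model would use the months observed and rely on missing at random, as {20c} says.
- **Safety oversight does not run through this model.** Falls prompt individual interviews, and the joint committee reviews adverse events every 3 months ({22}). That is correct, so the point concerns the outcome comparison and not participant monitoring.

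**Conclusion.** The point holds as an over-broad rule. On its wording, {20a} gives falls a linear model of mean change adjusted for baseline score, which does not suit a prospectively recorded and mostly zero event outcome. The consequences are poor fit, no direct handling of differing follow-up time, and some loss of efficiency, chiefly where follow-up is unequal. Neither invalidity of the comparison nor impossibility of fitting is shown.

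The conclusion rests on the Discussion's listing of falls as a secondary outcome and on falls being analysed as a number of events, which the Falls entry does not spell out. The sparsity figures rest wholly on assumed rates and dispersion. The effect is confined to one secondary outcome. It should be corrected before the SAP is finalised, but it does not touch the main result.

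**What to change.** 1. In {20a}, except falls from the linear rule, alongside the 400-m walk. State that the number of falls will be analysed with a count model, for example negative binomial regression with log follow-up time as offset and the same coach or cohort clustering, and reported as a rate ratio with its confidence interval.
2. Make the status of falls the same in Objectives {7}, the Falls entry and the Discussion. If it is secondary, add it to the list in {7}.
3. Leave the covariates and the analysis windows to the SAP.

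The cost is a sentence or two in {20a} and one entry in {7}. The monthly calendars already provide the data, and neither the primary analysis nor the sample size changes.
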